### Sample size

There are several studies investigating change in per cent acid exposure from baseline while wearing the CPAP device. Sample sizes suggested from current data based on change in total acid were between 86 to 168 per group (excluding any attrition).^12 39^ Using the smallest effect size published (Tawk *et al*^12^), assuming a one-sided non-inferiority design with a margin of 4.15 (per cent total acid) together with an SD of 10.8 with a power of 90% and alpha of 2.5% for a definitive study, this would require a sample of 288 (without attrition). Considering the likelihood of the main study finding an effect of this size within a 80% CI, then an approach taken by Cocks and Torgerson^40^ requires a feasibility sample equivalent to approximately 9% of the proposed definitive sample requiring 26 participants. Accommodating an overall attrition rate, including tolerance to the devices, of 40% requires a sample of 44 to be randomised. A sample of 44 will also give us a 95% CI of +/−14% around the attrition rate.

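### The 9% pilot fraction matches a definitive trial with 80% power, but is applied to 288, a sample sized at 90% power; 26 and 44 do not follow from the stated inputs.

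*Protocol article*

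**What the plan says.** The Sample size section of the protocol article builds the randomised number in a chain.

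- The definitive trial is a one-sided non-inferiority comparison with a margin of 4.15 percentage points of acid exposure, "together with an SD of 10.8" and "with a power of 90% and alpha of 2.5% for a definitive study". The resulting total is 288 before attrition.
- The pilot criterion is introduced with the words "Considering the likelihood of the main study finding an effect of this size within a 80% CI". A cited approach then "requires a feasibility sample equivalent to approximately 9% of the proposed definitive sample requiring 26 participants".
- Overall attrition of 40% "requires a sample of 44 to be randomised".
- As an additional property, 44 participants are said to give a 95% CI of about ±14% around the attrition rate.

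The section does not say whether the 80% limit is one- or two-sided, what difference it is centred on, or how the 9% was obtained. The figure of 44 (22 per arm) is repeated in the Abstract, and the 22 per arm under Randomisation procedures and Interventions.

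**The concern.** A pilot fraction of this kind depends on the power of the definitive trial. The natural reading of the criterion is that the pilot's 80% confidence limit around a zero difference should exclude the non-inferiority margin. SD and margin then cancel from the ratio of pilot to main sample, leaving only the confidence level of the pilot and the alpha and power of the main trial. A fraction that is right for one power is wrong for another. The 9% looks like the 80%-power value, whereas the 288 it multiplies was sized at 90% power.

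At stake is whether the stated derivation supports the randomised number. Participants undergo transnasal monitoring overnight on two occasions, so the reason given for their number should be reproducible.

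**Working it through.** **Inputs, all from the Sample size section:** margin 4.15; SD 10.8; power 90%; one-sided alpha 2.5%; total 288; pilot confidence level 80%; pilot fraction about 9%; attrition 40%. Allocation is 1:1 (Study design). **Assumption:** the true difference is zero; the section gives no other value.

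**1. The plan's own figures.**
- Main trial, normal formula: n per arm = 2 × [(1.9600 + 1.2816) × 10.8/4.15]² = 142.3, so 143 per arm and 286 in total. The noncentral t version gives 144 per arm, exactly 288. At 80% power the total would be 214 (normal) or 216 (t). The 288 is therefore a 90%-power figure.
- Pilot: 0.09 × 288 = 25.9, so 26.
- Attrition: 26/0.6 = 43.3, so 44.
- Precision: 1.96 × √(0.4 × 0.6/44) = 14.5%, consistent with the printed ±14%.

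Every step reproduces except the 9% itself.

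**2. The fraction, one-sided 80% limit.** The limit around zero reaches the margin when n per arm = 2 × (z_CI × SD/margin)². Dividing by the main-trial formula gives

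fraction = [z_CI/(z_0.975 + z_power)]².

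- 80% power: [0.8416/(1.9600 + 0.8416)]² = 9.02%; × 288 = 25.99.
- 90% power: [0.8416/(1.9600 + 1.2816)]² = 6.74%; × 288 = 19.4, so 20.

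**3. Check without any fraction.** Directly from SD and margin, n per arm = 2 × (0.8416 × 10.8/4.15)² = 9.6, so 10 per arm and 20 in total. With a t quantile it is 11 per arm, 22 in total. This result does not depend on the main trial's power. Randomised: 20/0.6 = 33.3, so 34; 22/0.6 = 36.7, so 37, or 38 for equal arms.

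**4. What 26 completers give.** SE = 10.8 × √(2/13) = 4.236.
- The one-sided 80% limit is 0.8416 × 4.236 = 3.57 (about 3.63 with t), inside 4.15.
- The margin lies at 4.15/4.236 = 0.98 standard errors. The one-sided limit that just reaches it is 83.6% (normal) or 83.1% (t, 24 df).

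**5. Two-sided 80% interval.** The quantile becomes 1.2816.
- Fraction at 90% power: [1.2816/(1.9600 + 1.2816)]² = 15.6%; × 288 = 45.0.
- Directly: n per arm = 2 × (1.2816 × 10.8/4.15)² = 22.2, so 23 per arm and 46 in total; 46/0.6 = 76.7, so 77 randomised.
- With 26 completers the half-width is 1.2816 × 4.236 = 5.43, outside 4.15.

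**6. Another alpha.** One-sided alpha 5% with 90% power and a one-sided 80% limit gives 8.3%; × 288 = 23.8. This does not give 26 either.

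| Reading of the 80% limit, at 90% power | Fraction | Completers | Randomised |
|---|---|---|---|
| One-sided | 6.7% | 20 (22 with t) | 34 to 38 |
| Two-sided | 15.6% | about 46 | about 77 |
| As printed | about 9% | 26 | 44 |

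**The case against.** The strongest reply is that the criterion checked here is inferred. The section mentions an 80% CI and a cited approach; it does not mention a zero difference, a one-sided limit or the ratio formula. What the cited source prescribes cannot be checked from the document. This stands, and it is why the result has to be given for both sidednesses. It does not rescue the 9%: no reading above at the stated 90% power returns 26, while the one-sided 80%-power fraction returns 25.99.

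A second reply is that on the one-sided reading 26 completers satisfy the criterion with a few to spare, so nothing is lost. That also stands, and it limits the severity. But the text presents 26 as what the approach requires, not as a deliberate excess, and on the two-sided reading the direction reverses.

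A third reply is that 44 has its own support in the precision of the attrition rate. This is correct: that figure is printed and holds. In addition, the Statistical analysis section plans estimates with 95% CIs and no hypothesis tests, so no analysis described there uses the 80% limit.

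A reader might infer that the mistake would carry over into sizing the definitive trial. The document does not support that. A pilot-to-main fraction is not an input to the main sample size, and the aims at the end of the Introduction say that this will come from the estimated effect on the primary outcome.

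**Conclusion.** Wrong as written, but minor. A fraction that fits 80% power is multiplied by a sample sized at 90% power, and the resulting 26 and 44 do not follow from the stated inputs.

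The size and direction depend on a point the section leaves open. If the limit is one-sided, the completers needed are 20 to 22 against 26, and the error is conservative. If it is two-sided, about 46 are needed and 26 falls short. Both results assume a zero true difference and a criterion that the limit must exclude the 4.15 margin.

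A reader might conclude that the trial is simply oversized and should randomise 34 to 38. The document does not support that: it does not fix the one-sided reading, and 44 is justified separately by attrition precision, which would widen to about ±16.5% with 34 (1.96 × √(0.24/34)) or ±15.6% with 38.

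**What to change.** Revise the pilot-fraction text in the Sample size section so that it:

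- states whether the 80% limit is one- or two-sided and what it must achieve (for example, that the limit around a zero difference excludes the 4.15 margin);
- either replaces the 9% with the fraction for 90% power (about 6.7% one-sided, about 15.6% two-sided) or, if the limit is one-sided, says that 9% is the 80%-power fraction used as a conservative figure;
- states what 26 completers actually give: a one-sided limit of about 83 to 84% just reaches the margin;
- rests the 44 on the precision of the attrition rate, about ±14%.

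The cost is a few sentences. Recruitment and the planned analyses stay as they are.

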### Statistical analysis

Baseline characteristics will be summarised for all participants within the trial arms.

The feasibility outcomes include:

Percentage of screened patients who were eligible for the trial.Percentage of eligible patients who agreed to participate.Percentage of patients who completed the trial.

We will then assess one clinical outcome to assess signal of efficacy, which is the change in percentage acid contact time pH <4 with the device in situ. Participants’ uptake of and adherence to both CPAP and MAD, as well as follow-up rates, will be summarised and presented as percentages. Although determining differences in clinical outcomes between the arms is not the primary purpose of this feasibility study, comparisons will be undertaken to investigate the feasibility of studying these outcomes and to calculate potential estimates and 95% CIs. As recommended in guidelines for good practice for the analysis of pilot studies,^41^ the focus of the results will be on the estimates of the treatments rather than statistical significance and as such no hypothesis testing will be undertaken. Differences between the two comparison groups will be presented in the form of an unadjusted mean difference for continuous outcomes, and an OR for binary outcomes, with their associated 95% CIs. These comparisons will be made on an intention to treat basis with consideration given to per protocol analysis as sensitivity. While every effort will be made to minimise missing data, assessment of the levels of missing data will indicate suitability of measures to be continued into the definitive trial.

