##### Primary clinical outcome to signal efficacy and inform a definitive power calculation

Change in percentage acid contact time pH <4 with the device in situ measured using nocturnal data from 24-hour pH monitoring at initial gastroenterology screening visit and follow-up gastroenterology assessment post-therapy.

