### Inclusion/exclusion criteria

Patients will be included in the study if they are:

Aged 18 or over.Confirmed OSA with Apnoea-Hypopnoea Index score between 10 and 50,Confirmed GORD with greater than 6% of acid exposure time <pH 4 over 24 hours.No previous CPAP or MAD therapy.Sufficient healthy teeth to support an MAD, that is, 10 teeth in each jaw, no periodontal pockets >5, no frank cavitation or loose crowns/bridges.Willing and able to provide informed consent to the study.

Patients will be ineligible if:

Pregnant or breast feeding.Unable or unwilling to stop GORD medication 2 days prior to assessment or unable to undergo manometry and pH impedance testing.Known liver disease or oesophageal/gastric varices.Previous surgery or intervention for reflux such as fundoplication, which may preclude pH impedance testing.Any previous treatment for oesophageal neoplasia.Unable/unwilling to tolerate either a CPAP mask or an MAD,Medical history likely to impact on 24-hour impedance testing, for example, bulimia nervosa,Participation in other research within previous 30 days.

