### Randomisation procedures

Participants who meet the inclusion/exclusion criteria will be allocated 1:1 using fixed-block randomisation by the purpose-built computer-generated randomisation service provided by King’s Clinical Trials Unit (KCTU) to either the CPAP (n=22) or the MAD (n=22) arm. Once the participant identifier is entered into the system, an e-mail will be sent to the principal investigators and trial manager informing them of the allocation.

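### Continuous outcomes are compared by an unadjusted mean difference although each has a baseline; adjusting for it would give a modestly narrower interval at almost no cost.

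*Protocol article*

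**What the plan says.** In the protocol article, the section Statistical analysis fixes the form of the comparison: "Differences between the two comparison groups will be presented in the form of an unadjusted mean difference for continuous outcomes". The result is given with a 95% CI and without a hypothesis test. No baseline-adjusted estimate appears anywhere in the article.

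The clinical outcome it applies to is "Change in percentage acid contact time pH <4 with the device in situ measured using nocturnal data", taken at the screening visit and again after therapy. The same screening recording decides entry: "Confirmed GORD with greater than 6% of acid exposure time <pH 4 over 24 hours". Everyone randomised should therefore have a baseline. The Secondary outcome measures section also lists the Reflux Symptom Index, Epworth Sleepiness Scale, Leicester Cough Questionnaire and three quality-of-life instruments, each recorded at baseline and after the intervention.

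Under Randomisation procedures, participants are "allocated 1:1 using fixed-block randomisation". No stratification by acid exposure is stated. The heading of the clinical outcome gives its purpose as signalling efficacy and informing the definitive power calculation.

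**The concern.** The word unadjusted is a positive choice, not a detail left to an analysis plan, and the article gives no reason for it. A change score uses the baseline, but with a fixed coefficient of 1. When the correlation between visits is below 1 and the SDs are equal, that coefficient is too large: the arm that happens to start higher tends to fall more, whatever the device. Regression on baseline (ANCOVA) estimates the coefficient instead.

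With about 13 per arm and no stratification on acid exposure, chance imbalance of some size is likely. The study puts its emphasis on estimates and intervals, so what is at stake is the width of the interval and how far one particular estimate is moved by imbalance. The spread that is passed on to the definitive design is also affected.

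**Working it through.** **Inputs from the Sample size section.** The definitive design is set out "with a margin of 4.15 (per cent total acid) together with an SD of 10.8 with a power of 90% and alpha of 2.5" per cent, giving 288 in total. The feasibility sample is "approximately 9% of the proposed definitive sample requiring 26 participants", that is 13 per arm, raised to 44 randomised for 40% attrition.

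**Reproducing the plan's figures.**
- Normal approximation: 2 × (1.960 + 1.282)² × 10.8² / 4.15² = 142.3, so 143 per arm, 286 in total. The noncentral t version gives 144 per arm, exactly 288.
- 9% of 288 = 25.9, rounded to 26.
- 26 / 0.6 = 43.3, rounded up to 44.

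The stated sizes hold, and 13 per arm is the planned number with follow-up.

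**Assumptions.** The article does not say whether 10.8 is the SD of change or of a single measurement; it is taken as the SD of change. The SD σ is taken as equal at both visits. The correlation ρ is not given, so 0.3, 0.5, 0.7 and 0.9 are shown.

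**Precision.**
- Variance of change: 2(1 − ρ)σ². Residual variance after adjustment: (1 − ρ²)σ². Their ratio is (1 + ρ)/2 = 0.65, 0.75, 0.85, 0.95.
- Unadjusted: SE = 10.8 × √(2/13) = 4.24. Half-width = 2.064 (t, 24 df) × 4.24 = 8.74.
- Adjusted: residual SD = 10.8 × √((1 + ρ)/2). The variance is multiplied by about 1 + 1/(26 − 4) = 1.045 for estimating the slope, and t has 23 df (2.069).

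| ρ | Residual SD | Adjusted half-width | Narrower by |
|---|---|---|---|
| 0.3 | 8.71 | 7.22 | 17% |
| 0.5 | 9.35 | 7.76 | 11% |
| 0.7 | 9.96 | 8.26 | 6% |
| 0.9 | 10.53 | 8.73 | about 0% |

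**Chance imbalance.** The between-arm baseline difference has a standard error of √(2/13) = 0.39 SD, and the probability that it exceeds 0.5 SD in either direction is about 20%. Given a baseline difference D, the expected difference in change is the treatment effect minus (1 − ρ)D.

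For consistency with 10.8 as the SD of change, the baseline SD must be 10.8 / √(2(1 − ρ)) = 9.1, 10.8, 13.9 at ρ = 0.3, 0.5, 0.7. The shift from a one-standard-error imbalance is then:
- ρ = 0.3: 0.7 × 9.13 × 0.392 = 2.5 points
- ρ = 0.5: 0.5 × 10.8 × 0.392 = 2.1 points
- ρ = 0.7: 0.3 × 13.94 × 0.392 = 1.6 points

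Against the margin of 4.15 these are about 60%, 51% and 40%.

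**The case against.** The strongest reply is that this is a feasibility study. Its primary outcomes are screening, randomisation and completion percentages, and the article says that differences between arms are not its main purpose. The unadjusted difference is unbiased over randomisation, and its interval already allows for chance imbalance. All of this stands: the loss is in precision, not validity. It would be wrong to treat the acid-time comparison as the whole clinical output of the trial, since reflux symptoms, sleepiness, cough, wear time and quality of life are reported too.

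A reader might infer that selecting patients on high acid exposure biases the comparison through regression to the mean. The documents do not support that. Eligibility rests on exposure over 24 hours and the outcome on nocturnal data, so selection on the nocturnal baseline is indirect. It also precedes randomisation and acts on both arms alike in expectation.

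A reader might also infer that the definitive 288 is too large because of this sentence. That does not follow. The 288 rests on published figures, and a smaller number would need the definitive trial itself to be analysed with baseline adjustment. It could choose that whatever is reported here. Moreover, an SD estimated on 24 df has a 95% interval of roughly 0.78 to 1.39 times its value (10.8: 8.4 to 15.0), which is wider than the effect of adjustment on the SD.

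Finally, 13 per arm assumes the full 40% loss. If participants who cannot tolerate a device are still re-tested under intention to treat, the number lies between 13 and 22 per arm. At 22 the unadjusted half-width is about 6.6.

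**Conclusion.** The point holds as a recommendation on efficiency. The planned estimate is valid but less precise than the data allow, and it keeps (1 − ρ) of any chance baseline imbalance. At the planned 13 per arm the 95% interval would be 17%, 11% or 6% narrower at ρ of 0.3, 0.5 or 0.7, and no narrower near 0.9. A one-standard-error imbalance moves the unadjusted estimate by about 2.5, 2.1 or 1.6 points.

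These sizes depend on an unstated correlation, on 10.8 being the SD of change, and on equal SDs at the two visits. If treatment reduced the follow-up SD, for example to 0.7 of baseline (an assumption), the large-sample variance ratio σ²(0.49)(1 − ρ²) / σ²(1 + 0.49 − 1.4ρ) would be 0.42, 0.47 or 0.49 at the same three correlations, and the gain would be larger. The direction of the advice is secure; its size is not known.

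**What to change.** In Statistical analysis, replace the unadjusted mean difference as the main estimate for every continuous outcome with a baseline (acid contact time, Reflux Symptom Index, Epworth score, cough, quality of life). Use instead the between-arm difference from a linear regression on arm and the baseline value of the same measure, with its 95% CI. Keep the unadjusted difference as a secondary result.

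Report the residual SD and the observed baseline to follow-up correlation, so that the definitive trial can be sized for a baseline-adjusted analysis if it adopts one.

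The cost is one sentence and one degree of freedom per outcome, with no new data.

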## Discussion

Given the increasing prevalence of both OSA and GORD, it is important to further investigate the inter-relationship between the conditions and the impact of OSA treatment on GORD. While there is evidence that CPAP reduces GORD, the effect size is unclear, and the impact of MADs on GORD is entirely un-investigated.

This feasibility trial is designed as a first step to provide this important information for patients deciding on treatment choices and the prescribing sleep clinician. This trial will give us insights into the feasibility for testing patients, patient experience, the mechanism of action and the overall effect. There were several items for consideration when developing the study design. First, we chose to use a level 2 sleep study rather than polysomnography. This was because a level 2 device is sufficient for diagnosis of OSAS provided no other respiratory/sleep pathologies are suspected. At the time of recruitment, all participants had been assessed by their managing consultant and diagnosed as having suspect OSAS. The primary outcome of this study is a gastroenterology outcome and AHI is used solely as the inclusion criteria. Furthermore, the final assessment night for the patient will necessitate them to wear a sleep study device, a nasal pH monitor and their MAD or CPAP therapeutic intervention. We thought this would be easier for the patient if done at home. Finally, we would like the definitive trial to be a multicentre trial. Not all centres will have capacity for polysomnography. For these reasons, we deemed that a Watch-PAT was appropriate. We have also considered items such as the interference of the nasal catheter with the CPAP mask. This has been extensively discussed with our PPI group, some of whom have already undergone 24-hour pH monitoring while wearing their CPAP. The mask seal can be maintained with strategic placement of the nasal catheter and tape. There is also precedent for this in previous studies.^12 16^ However, the feasibility of this will be explored.

We will also explore health economic measures to best capture the cost of services versus the value obtained for patients and healthcare providers. From a UK NHS perspective, both CPAP and MADs are reported to be similarly cost-effective treatments.^18^ This may change once their efficacy on the management of nocturnal gastro-oesophageal reflux is assessed. Investigation into the health economic feasibility for other funding systems is beyond the scope of this initial feasibility paper. However, we will be informing on the best measures to capture health economic outcomes, which can then be used in different healthcare funding environments.

### Patient and public involvement statement

The trial was designed to generate evidence for patients with both OSA and GORD who are deciding on their treatment options. Our patient coapplicant is highly active within the OSA community with both feedback and dissemination means at a national level (Hope2Sleep Charity). We have an active PPI group who were also involved in the review and development of study protocol and patient information sheets. Patient advocacy is an important part of our oversight committee and our patient coapplicant is in charge of ensuring that the patient perspective is presented throughout the duration of the trial lifecycle. All findings from the study will be made available for dissemination to the public.

## Ethics and dissemination

Health Research Authority approval has been obtained from the Nottingham 2 Research Ethics Committee, ref:22/EM/0157 and the trial has been registered on ISRCTN (https://doi.org/10.1186/ISRCTN16013232) with access to the full protocol. Definitive findings about the feasibility of doing 24-hour pH oesophageal monitoring while doing a home sleep study will be disseminated via clinical and research networks facilitating valuable insights into the simultaneous management of both conditions.
